#### Eligibility criteria

##### Inclusion criteria

At enrollment, the volunteer children must fulfill all of the following eligibility criteria to be considered for inclusion: (1) age at least 8 years and ≤ 18 years (regardless of race, ethnicity, gender); (2) FAP-NOS or IBS diagnosed according to the Rome IV Criteria [2]; (3) baseline average pain intensity at least 30 mm on a 100-mm Visual Analogue Scale (VAS) [9]; (4) feeding via the oral route; (5) ability to read and comprehend any employed questionnaires/scales; (6) signed informed consent; and (7) stated availability throughout the study period.

Participants with IBS and a stool consistency score > 5 on the Bristol Stool Scale will be classified as having IBS with predominant diarrhea (IBS-D); if the stool consistency score is < 3, the subjects will be classified as having IBS with predominant constipation (IBS-C) [16].

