##### Study procedure and timeline

For the study procedure and timeline, see Table 1 and Fig. 1. At the initial baseline visit (Visit 0), children will be diagnosed with IBS or FAP-NOS by a gastroenterologist, undergo a growth assessment by a nurse, and have an initial visit with a research dietitian. At the initial dietary consultation, all subjects will receive oral and written information regarding the study. A Monash FODMAP-trained dietitian will educate the caregiver and child about the principles of the study design, as well risks and benefits, during a face-to-face meeting. The subjects will be asked to complete a questionnaire, reflecting the preceding week, including questions about the intensity and frequency of abdominal pain, stool consistency, absence from school, and parents’ absence from work. Baseline scores on the Gastrointestinal Symptom Rating Scale (GSRS) [21], the KIDSCREEN-10 index [22] and the World Health Organization Five Well-Being Index (WHO-5) [18] will also be obtained. The child’s anthropometric measurements will be obtained by an independent nurse (see Growth in Outcome section). The baseline dietary assessment will include a qualitative and quantitative assessment of each child’s usual food intake based on a 3-day food record completed retrospectively, against the Nutrition Standards for the Polish population (2017) [23]. Based on the same food record, the baseline FODMAP intake in each meal also will be calculated using the Monash FODMAP Calculator. The dietitian will perform a thorough interview to tailor the diet to the individual child’s needs [19, 24, 25]. The baseline physical activity level also will be assessed using a Moderate-to-Vigorous Physical Activity (MVPA) screening measure [26].

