#### Outcomes

In agreement with recommendations [16], one primary outcome was pre-specified:
**Change in abdominal pain intensity.** Responders will be those with a daily reduction in the intensity of abdominal pain episodes of at least 30% at week 4 compared with baseline, and this value should be at least equal to the Reliable Change Index (RCI) for that sample [16, 27]. A cut-off of 25 mm for RCI change was adopted [16]. This outcome also will be assessed as the change at weeks 1, 2, and 3 from baseline.

For participant timeline, see Table 1.

Secondary outcomes to be assessed during the 4-week intervention, following the standardized core outcome set [17], will be:

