**Change in stool consistency.** Responders will be subjects with improvement in their average stool consistency during the last week of the trial compared with baseline [≥1 higher Bristol Stool Scale score in case of IBS-C, or at least one lower score in case of IBS-D] [16]. The change at weeks 1, 2, and 3 from baseline also will be measured.**Change in abdominal pain frequency** at weeks 1, 2, 3, and 4 from baseline [16].**Change in GSRS** [21] **total score** at weeks 1, 2, 3, and 4 from baseline.**Change in KIDSCREEN-10 index** [22] **total score** at weeks 1, 2, 3, and 4 from baseline.**Change in WHO-5** [18] **total score** at weeks 1, 2, 3, and 4 from baseline.**Change in percentage of school attendance** associated with IBS symptoms (at weeks 1, 2, 3, and 4 from baseline).**Change in percentage of parents’ work absenteeism** associated with IBS symptoms in child (at weeks 1, 2, 3, and 4 from baseline).**Change in BMI-for-age z-score**. The BW (kg) and standing height (cm) will be measured following standard methods by an independent nurse at baseline, after 2 weeks, and after 4 weeks. Body Mass Index (BMI) will be calculated using the standard eq. BMI-for-age z-score will be computed using the WHO AnthroPlus software v1.0.4., then assessed and monitored over time using the WHO growth charts by a dietitian.**Percentage of compliant participants** (see Compliance section).**Percentage of tolerability of the low-FODMAP diet.** This outcome will be reported as a mean for each study group, and as a comparison between groups (MD [mean difference] with 95% CI).**Adverse events.** The number of all adverse events and the number of participants reporting adverse events associated with the intervention (with characteristics) will be reported for each study group (see Criteria for discontinuing the intervention and Harms sections).

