#### Data analysis

All analyses will be conducted on an intention-to-treat basis, including all patients in the groups to which they are randomized for whom outcomes are available (including dropout and withdrawals). Per-protocol analysis also will be performed, in which all subjects who finish the study according to the protocol will be included.

Descriptive statistics will be used to summarize baseline characteristics. The Student t-test will be used to compare mean values of continuous variables approximating a normal distribution. For non-normally distributed variables, the Mann-Whitney U test will be used. The x^2^ test or Fisher exact test will be used, as appropriate, to compare percentages. The same computer software will be used to calculate the relative risk (RR), number needed to treat (NNT), and mean difference (MD), all with a 95% confidence interval (CI). The difference between study groups will be considered significant when the *p* value is < 0.05, when the 95% CI for RR does not include 1.0, or when 95% CI for MD does not include 0. All statistical tests will be two-tailed and performed at the 5% level of significance.

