#### Methods of additional analyses

Both the primary and secondary outcomes will be analyzed by logistic regression, controlling for three, prespecified, potential confounding variables, i.e., age, sex, and subtype of IBS. The difference between study groups will be considered significant when the *p* value is < 0.05, when the 95% CI for RR (or odds ratio [OR]) does not include 1.0, or when 95% CI for MD does not include 0. All statistical tests will be two-tailed and performed at the 5% level of significance.

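### Baseline values collected at Visit 0 are covariates in no analysis, although the 25-mm floor ties response to baseline VAS: a loss of precision and of protection against chance imbalance, not a bias

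*Protocol article*

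**What the plan says.** The Data analysis section of the protocol article fixes two-sample tests without covariates: "The Student t-test will be used to compare mean values of continuous variables approximating a normal distribution", Mann-Whitney U where normality fails, and chi-square or Fisher for percentages. It plans RR, NNT and mean difference with 95% confidence intervals.

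Methods of additional analyses adds a logistic regression of both primary and secondary outcomes. It controls for three prespecified "potential confounding variables, i.e., age, sex, and subtype of IBS". No baseline outcome value is on that list. The section on sequence generation rules out stratification.

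The baselines exist. At Visit 0 the child completes a questionnaire "including questions about the intensity and frequency of abdominal pain, stool consistency, absence from school, and parents’ absence from work", and baseline GSRS, KIDSCREEN-10, WHO-5 and anthropometry are also obtained (Study procedure and timeline).

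The primary responder rule under Outcomes requires a fall of at least 30% from baseline at week 4 that is also no smaller than the Reliable Change Index: "A cut-off of 25 mm for RCI change was adopted". Children are eligible from an average baseline of 30 mm. Baseline does enter through subtraction: for pain intensity, "This outcome also will be assessed as the change at weeks 1, 2, and 3 from baseline", and most continuous secondary outcomes are changes "at weeks 1, 2, 3, and 4 from baseline".

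**The concern.** A responder must satisfy a relative and an absolute condition. Where the absolute one binds, a child with mild pain needs a far larger proportional fall than a child with severe pain. Baseline VAS is thus built into the definition of response and can be expected to predict it, yet the covariate list names three other variables and leaves it out. Because the article closes that list, the omission is a stated choice and not a detail left to an analysis plan.

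Two things are at stake. With 74 children and no stratification, the arms may differ in baseline VAS by chance, and nothing in the design or analysis would absorb the effect on the estimated responder difference. For continuous outcomes, a t-test on change scores or on week-4 values gives up precision that the baseline measurement could supply. The planned adjusted analysis is no remedy there, because logistic regression does not suit continuous scores such as GSRS, KIDSCREEN-10, WHO-5 or BMI z-score.

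**Working it through.** **1. Where the floor binds** (inputs: 30 mm entry limit, 30% and 25 mm, all from the article). Required proportional fall = max(25, 0.30 × B) / B for baseline B. The two conditions meet at 25 / 0.30 = 83.3 mm.

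| Baseline (mm) | Required fall |
|---|---|
| 30 | 25/30 = 83.3% |
| 40 | 25/40 = 62.5% |
| 50 | 25/50 = 50% |
| 60 | 25/60 = 41.7% |
| 80 | 25/80 = 31.2% |
| 83.3 and above | 30% |

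**2. Assumptions for everything below.** The article gives no mean, SD or correlation for VAS. Assumed: baseline normal with mean 55 and SD 18, truncated to 30-100 mm; week-4 SD 22; mean fall of 15 mm in controls; diet effect 0 or 15 mm; 31 per arm; nominal correlation r of 0.3, 0.5 or 0.7 (0.25, 0.44 and 0.64 after truncation). About 94% of simulated children then lie below 83.3 mm. The article's 31 per arm cannot be reproduced without a control rate or SD, but this point does not depend on it.

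**3. Response by baseline, no diet effect.** From the 30-40 mm band to the 84-100 mm band, control response rises from 15% to 69% (r = 0.3), from 18% to 53% (r = 0.5) and from 21% to 33% (r = 0.7).

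**4. Chance imbalance.** The truncated baseline SD is about 15.1 mm. The SE of the difference in baseline means is 15.1 × √(2/31) = 3.8 mm, so an imbalance of more than 5 mm in either direction occurs in about 19% of trials (about 15% with 37 per arm). With no diet effect, 5 mm shifts the responder difference by about 5, 4 and 1 points at r = 0.3, 0.5 and 0.7. For scale, the SE of that difference is √(2 × 0.25 × 0.75 / 31) = 11 points at 25% response and √(2 × 0.40 × 0.60 / 31) = 12 points at 40%.

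**5. Binary primary outcome** (2,000 simulated trials per setting).

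| r | Power, chi-square | Power, logistic with baseline VAS |
|---|---|---|
| 0.3 | 0.55 | 0.58 |
| 0.5 | 0.69 | 0.70 |
| 0.7 | 0.85 | 0.84 |

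Type I error of the unadjusted tests (chi-square and both t-tests) was 0.048 to 0.059.

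**6. Continuous VAS, same simulation, 15-mm effect.**

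| r | t-test, change | t-test, week 4 | ANCOVA |
|---|---|---|---|
| 0.3 | 0.70 | 0.75 | 0.77 |
| 0.5 | 0.82 | 0.79 | 0.86 |
| 0.7 | 0.96 | 0.82 | 0.96 |

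**7. Continuous outcomes with equal variances at both times.** Var(ANCOVA) / Var(change) = (1 + r)/2, which is 0.65, 0.75 and 0.85. So 31 per arm becomes 31 × 0.65 = 20.2 (21), 31 × 0.75 = 23.3 (24) and 31 × 0.85 = 26.4 (27). Equivalently, 80% power becomes Φ(2.80/√0.65 − 1.96) = 94%, and likewise 90% and 86%. Against week-4 values alone the ratio is 1 − r², a saving of 9%, 25% and 49%.

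**The case against.** A reader might infer that baseline VAS is not used at all. That is wrong: it sets eligibility, is the reference for the responder rule, and enters the change scores. A t-test on change uses the baseline, only less efficiently than ANCOVA. Nor is every analysis unadjusted, since age, sex and IBS subtype are controlled for in the additional analyses.

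A reader might also infer that the primary result is biased or its error rate inflated. It is not. Randomisation already allows for chance imbalance, and simulated type I error stays near 5%. A 4-point shift is about a third of one standard error, and adjustment adds almost no power for the binary outcome.

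The 25-mm floor is a deliberate definition attributed to cited recommendations. That response depends on baseline is a consequence of that choice, not an error in it. The precision figures rest on assumed SDs and correlations, and with unequal variances the gain over change scores at r of 0.5 to 0.7 is small. Adjustment cannot use an own baseline for tolerability, which is rated only while on the study diet. Making a conditional odds ratio primary would not fit the planned RR and NNT.

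All of this stands, and it limits the point without removing it. Covariates are often left to an analysis plan, but here the article names a closed list of three, and baseline values are not on it.

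**Conclusion.** The point holds as one of efficiency and of protection against chance imbalance. The article collects baseline values and then uses none as a covariate, and the adjusted model it names does not fit continuous scores. The dependence of the required fall on baseline is plain arithmetic and needs no assumption.

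The sizes do need assumptions. For the responder difference, about 1 to 5 points per 5 mm of imbalance at correlations of 0.7 to 0.3. For power on the binary primary outcome, a negligible change (about -1 to +3 points). For continuous outcomes, about 0 to 8 points of power over change scores with unequal variances, and 6 to 14 points (from 80% to between 86% and 94%) with equal variances. The documents do not support a claim of bias, of an invalid test, or of a wrong responder definition. The change is worth making because it costs nothing in data collection and the trial is small.

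**What to change.** In Data analysis: for each continuous outcome with a baseline (VAS, pain frequency, GSRS, KIDSCREEN-10, WHO-5, BMI-for-age z-score), replace the two-sample test by ANCOVA on the week-4 value with that outcome's baseline as covariate. Leave tolerability as a plain between-group comparison.

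In Methods of additional analyses: specify linear models for continuous outcomes, and add continuous baseline VAS to the prespecified covariates of the responder model.

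Keep RR and NNT as the primary effect measures. If they are adjusted, obtain them by standardisation from the model and do not report a conditional odds ratio alone. The responder rate under the 30% condition alone is an optional sensitivity analysis, useful because the 25-mm condition decides for most baselines.

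The cost is wording only, as the baselines are already obtained at Visit 0. The change should be fixed before outcome data are examined, because a covariate added after an imbalance is seen would look post hoc.

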#### Sample size

The primary outcome is the reduction in the abdominal pain intensity in the low-FODMAP diet group compared with the regular diet group over the 4-week intervention. We assumed a 30% difference as being a clinically significant primary endpoint [16]. We estimate that 31 children in each group are needed to achieve a significant difference with a power of 80%, along with a two-sided 5% significance level. Given the anticipated dropout rate of 20%, we estimate 37 subjects are necessary in each study arm. Sample size calculations were performed with StatsDirect (StatsDirect Ltd. StatsDirect statistical software. http://www.statsdirect.com. England: StatsDirect Ltd. 2013).

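### For non-normal continuous outcomes the plan accepts either a rank-test p-value or a mean-difference interval as proof of significance, so read literally the type I error is about 6–7%, not 5%

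*Protocol article*

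**What the plan says.** The Data analysis section of the protocol article gives four statements that meet on each continuous outcome.

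- Choice of test: "The Student t-test will be used to compare mean values of continuous variables approximating a normal distribution". Then: "For non-normally distributed variables, the Mann-Whitney U test will be used".
- Effect measure: relative risk, number needed to treat and mean difference (MD) are to be calculated with 95% intervals. The MD is the only one of these for a continuous outcome, and it is not confined to normal variables. No median or Hodges-Lehmann difference is named to go with the rank test.
- Decision rule: "The difference between study groups will be considered significant when the *p* value is < 0.05", and further "when the 95% CI for RR does not include 1.0, or when 95% CI for MD does not include 0".
- Level: "All statistical tests will be two-tailed and performed at the 5% level of significance".

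The Outcomes section ties tolerability, a daily 100-mm VAS, explicitly to an MD with 95% CI. No section says which criterion prevails when the p-value and the interval point different ways. Methods of additional analyses repeats the decision sentence, including "or when 95% CI for MD does not include 0", but for logistic regression.

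**The concern.** For a t-test, p < 0.05 and a 95% MD interval that excludes 0 are the same event, so joining them by 'or' is harmless. For Mann-Whitney they are not. The rank test asks whether values in one arm tend to be larger; the MD interval asks whether the means differ. A non-normal outcome therefore has two routes to significance, each with an error of about 5%, and the combined error must be larger than either. That conflicts with the stated 5% level.

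The second consequence is in reporting. A result may be called significant on the rank p-value while the published MD interval includes 0, or the reverse, and the rule settles each such conflict in favour of significance. The outcomes most exposed are weekly pain episodes, school or work days missed, and the tolerability score, which are counts or bounded scores.

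**Working it through.** **Inputs from the protocol article.** Two-sided 5% level, the two tests, the MD with 95% CI and the 'or' rule (Data analysis); evaluable size per arm (Sample size: "We estimate that 31 children in each group are needed") and 37 per arm randomized; 1:1 allocation (Trial design).

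**Assumptions.** The article gives no distributions or SDs and names no normality check. The distributions below are therefore assumed. A variable was treated as non-normal if Shapiro-Wilk gave p < 0.05 in either arm. The MD interval was the pooled t interval. There were 20,000 null trials per scenario; the Monte Carlo standard error is √(0.05 × 0.95 / 20,000) = 0.0015, or 0.15 percentage points.

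**Formula.** Let T be the event that the MD interval excludes 0, and M the event that Mann-Whitney gives p < 0.05. When the rank test is in use, the rule rejects on T or M:

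P(T or M) = [P(T) + P(M) + P(T and M disagree)] / 2.

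Any disagreement thus adds half its frequency to the average error of the two tests.

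**Results, no true difference (% of trials; 31 per arm unless stated).**

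| Assumed distribution | MD interval (t) | Mann-Whitney | Test picked by data, p only | Either-or | Either-or, 37 per arm | T and M disagree |
|---|---|---|---|---|---|---|
| Normal | 5.09 | 4.58 | 5.05 | 5.21 | 5.32 | 1.92 |
| Exponential | 4.83 | 4.78 | 4.78 | 6.66 | 6.93 | 3.72 |
| Lognormal, σ = 1 | 4.21 | 4.73 | 4.73 | 6.80 | 7.09 | 4.66 |
| Lognormal, σ = 1.5 | 3.21 | 4.83 | 4.83 | 6.55 | 6.86 | 5.05 |
| t with 3 df | 4.40 | 4.78 | 4.91 | 5.97 | 6.26 | 3.30 |
| Negative binomial, mean 2, k = 0.5 | 4.61 | 4.83 | 4.83 | 6.98 | 6.92 | 4.52 |
| Days missed, 70% zero-inflated | 4.74 | 4.69 | 4.69 | 5.99 | 6.11 | 2.54 |
| Skewed change score | 5.18 | 5.17 | 5.41 | 6.83 | 6.64 | 3.64 |

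Hand check, exponential: (4.83 + 4.78 + 3.72) / 2 = 6.67, against 6.66 simulated. Negative binomial: (4.61 + 4.83 + 4.52) / 2 = 6.98. For t with 3 df and the change score the rule gives slightly less than the formula, because the normality check sends some trials (28% and 19%) to the t-test, where the two criteria coincide.

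**Reading the table.**
1. The stated 5% is reproduced, or undershot, by any single test: on the non-normal rows, over both sample sizes, 3.2–5.2% for the MD interval and 4.5–5.2% for Mann-Whitney.
2. The either-or rule gives 6.0–7.1% on the non-normal rows and 5.2–5.3% on normal data.
3. Letting the data pick the test, but judging by p alone, gives 4.5–5.4% over all rows and both sizes. The excess therefore comes from the 'or'.
4. On the non-normal rows T and M disagree in 2.5–5.5% of null trials; the top of that range is lognormal σ = 1.5 at 37 per arm.

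**Binary outcomes.** Exact enumeration at 31 and 37 per arm, with response rates from 10% to 70%, gives 1.3–5.6% for chi-square or Fisher. Adding the relative-risk interval by 'or' did not change any of these figures.

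**The case against.** The strongest defence is that the sentence lists what significance looks like for each statistic, one criterion apiece. The relative-risk clause cannot apply to a continuous outcome nor the MD clause to a binary one, and the section goes on to fix every test at 5%. On that reading no outcome is tested twice. This partly stands: it is a possible reading, and it works for the t-test with its own interval. It fails for Mann-Whitney beside an MD interval, because both a p-value and an MD then exist for the same outcome and the text sets no order between them.

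Several stronger inferences are tempting, and the document does not support them.

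- *Choosing the test from the data inflates the error.* It does not here; judged on p alone the error stays near 5%. No pretest is named either, and assigning tests to variables may properly be left to an analysis plan that is not shown.
- *The primary result is at risk.* The primary outcome is a responder percentage, tested by chi-square or Fisher, and its error is unchanged by the rule. The study hypothesis is worded as a lower mean pain score, so a mean-pain analysis, if made, would fall under the rule; the responder analysis does not.
- *Methods of additional analyses has the same defect.* It repeats the sentence but names no rank test.
- *Arms with equal means but different shapes show far larger contradictions.* Such arms truly differ, so a rank-test rejection there is not a false positive for no effect of diet, and the shapes would be pure assumption.
- *All secondary outcomes are affected.* Most are analysed as changes from baseline, and total-score changes that are near normal show almost no excess.

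**Conclusion.** The concern holds in limited form. Followed as written, the Data analysis rule does not keep the stated 5% level for continuous outcomes judged non-normal: the error is about 6–7%, an excess of one to two percentage points. A second simulation at 31 per arm, with skewed or count data, gave 6.2–6.8% for the either-or rule against 4.2–5.0% for each single test. The p-value and interval contradict each other in roughly 2.5–5.5% of null trials.

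These figures rest on the literal reading of 'or', on assumed distributions and on an assumed normality check. The outcomes concerned are mainly secondary. The inflation is modest, but a stated decision rule that conflicts with its own stated level should be corrected before the analysis.

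**What to change.** In Data analysis, name one analysis for each continuous outcome and take both the p-value and the 95% interval from it. The mean difference with Welch p-value and interval is a suitable choice, and such an estimate can be pooled directly over the imputed datasets foreseen under Missing data. Mann-Whitney with a Hodges-Lehmann interval would also be coherent. Delete the 'or' list, state that this single analysis decides significance, and label any other test as sensitivity analysis.

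A permutation p-value beside a bootstrap interval would not be a repair, since it again pairs two procedures. At 31 per arm under the null (percentile bootstrap; exponential, lognormal and negative binomial data) they disagreed in 1.6–2.6% of trials, and accepting either rejected in 6.3–8.1%.

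The cost is wording only; conduct and sample size do not change. If the mean difference is chosen, some power is lost for heavy-tailed or strongly skewed outcomes. With a pure shift of half a robust SD at 31 per arm, the t-test had 29% power against 39% for Mann-Whitney on t data with 3 df, and 31% against 54% on exponential data. If that matters for a given outcome, prespecify the rank-based pair for it instead.
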